### Data analysis

2.12

Qualitative data produced during the formative research, usability testing, and post- intervention feasibility assessment will be transcribed, cleaned, and coded by trained research assistants using the Atlas.ti 22 textual data analysis software program. A coding scheme will be developed for the textual data and applied by trained coders. In combination with memoing and structured queries, we will use the Atlas.ti 22 program to identify key themes associated with each of the focal areas. An emphasis will be placed on comments/themes related to the feasibility (acceptability, operability, potential sustainability, etc.) and future usability of the application by food pantry, food bank and emergency operations directors and staff.

The statistical plan will begin with exploratory analysis to examine broad trends and intervention effects from pretest score/intake to posttest score/intake. We will compare the change in FAST scores between intervention and comparison groups using cluster-level t-tests for normally distributed continuous changes or nonparametric Wilcoxon-Mann–Whitney tests for non-normal continuous changes. Then we will conduct linear mixed-effect models for confirmatory testing of intervention effects, with adjustments. T-tests will be used for normally distributed continuous variables and nonparametric Wilcoxon-Mann–Whitney tests for non-normal continuous variables. We will follow the exploratory analysis with multilevel mixed models. The mixed effects regression models will use change in pantry- and client-level scores over time as outcomes and will be modified to identify intervention effects as well as risk factors in regression analyses. Adjustments for client demographics (age, sex, education, etc.) and pantry-level variables (e.g., pantry size) will be considered. The clients’ “home” pantry will be treated as a random effect. It is possible that our client sample will use multiple food pantries, leading to possible contamination. Thus, we will calculate an overall intervention pantry exposure score and adjust our analyses. However, we anticipate contamination will be mitigated by giving app access to the 18 selected intervention pantry clients only. Posttest scores will be response variables in the models. The primary hypothesis is: compared with comparison pantries, client bags in intervention pantries will have a greater improvement (larger positive change) in FAST scores from pre-intervention to post-intervention. We will compare the mean change in FAST scores of participant bags from the intervention pantries to those from the comparison pantries. We expect that the SAFPAS intervention will result in a mean improvement (positive mean change) in FAST scores that is 12 FAST points better than the mean change in the comparison group.

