#### Client-facing features

2.8.1

Clients will be able to access the following app features:

*Volunteer application*: Clients can sign up to volunteer at their pantry through the app. Their “application” to volunteer will be reviewed by the pantry coordinator and can be accepted or rejected. If accepted, they will be able to view available timeslots and sign up for a shift.

*Pantry locator*: This feature will show clients where there are food pantries nearby. In addition to location, they can also view hours of operation, whether they are accepting new clients, whether volunteers are needed, and whether certain food items are in stock.

*Communications center*: Food pantries and city agencies will be able to push messages to clients in the communications center. These would include pertinent messages related to food pantry operations (e.g., closures due to weather) and emergency preparedness updates and information. This will allow clients to receive real-time updates on the status of their community food pantry.

*eChoice*: Clients will be able to use the app to create general food orders using the eChoice module (Figure 2). While clients will not be able to order specific foods, they will be able to order the types of desired food items (e.g., fresh, frozen, canned), select diet preferences in line with the USDA Dietary Guidelines for Americans (44) (e.g., heart healthy, vegetarian/vegan, Kosher, Halal, gluten free); and indicate food allergies. Pantries will be able to select which of these options are available to their clients. They will also have the option of selecting a pick-up date and time from choices identified by the pantry. While some pantries may not be able match client preferences, the data collected from these forms will be reported to the food bank and other stakeholders and will allow for better insight into what food types are most relevant in each community. This eChoice ordering system support client access to healthy choices, as it will allow clients to choose what foods fit their households the best based on their diet needs and preferences.

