### Sample size and power

2.11

A sample size calculation was conducted to assess the impact on Aim 3: the change in the healthfulness of client bags (primary outcome). The calculation was based a cluster-level t-test comparing the mean change in FAST scores of client bags at the intervention pantries to those at the comparison pantries. In our calculation, we used the reported mean change in FAST scores in comparison and intervention food pantries from the previous FSHP trial (7) with that hypothesis that there will be a trend toward increased FAST scores among intervention pantry clients compared to clients who are sampled from comparison pantries. Ultimately, sample-size assumed a difference in FAST Scores of 12 points, effect size of 0.8, intraclass correlation of 0.2, type I error of 5%, and power level set at 80%, to lead to a total sample size of 20 stores with 10 per arm and 18 clients per pantry (*n* = 360 at baseline). One pantry was added to each arm of the study to account for possible attrition, leading to the final sample size of 40 pantries. Similarly, we have added 3 clients per pantry to allow for potential drop out and still have necessary power based on our previous trial (7).

For direct comparison of the change in outcome over the intervention period, we will calculate an individual’s change in FAST score over time for each outcome by subtracting the pre-intervention value from the post-intervention value. These changes will then be compared between the intervention groups using cluster-level t-tests or nonparametric Wilcoxon-Mann–Whitney tests, depending on the normality of these individual changes.

The study is not powered to test for differences in secondary outcomes (e.g., nutrition knowledge, BMI, dietary intake, food pantry environment); initial findings will be used as preliminary data for a larger trial.

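### The confirmatory analyses are to be adjusted for clients' exposure to intervention pantries, which arises after allocation, and this is not confined to a sensitivity analysis

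*Protocol article*

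**What the plan says.** The Data analysis section gives the reason for the adjustment, "It is possible that our client sample will use multiple food pantries, leading to possible contamination", and then the remedy: "Thus, we will calculate an overall intervention pantry exposure score and adjust our analyses". It adds a mitigation: "However, we anticipate contamination will be mitigated by giving app access to the 18 selected intervention pantry clients only". The score is not defined, its timing is not given, and no analysis is exempted. By contrast, adjustment for demographics and pantry size is only to be considered.

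The same section ranks the analyses. The opening step is exploratory ("The statistical plan will begin with exploratory analysis to examine broad trends and intervention effects") and holds the cluster-level t-test or Wilcoxon-Mann-Whitney comparison of changes. The mixed models follow: "Then we will conduct linear mixed-effect models for confirmatory testing of intervention effects, with adjustments".

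The primary hypothesis is stated by allocated pantry: "compared with comparison pantries, client bags in intervention pantries will have a greater improvement (larger positive change) in FAST scores".

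**The concern.** The hypothesis asks what happens to clients' bags when their pantry is allocated to the app. A client's exposure to intervention pantries cannot exist until pantries have been allocated, so the score is a consequence of allocation and not a baseline characteristic. Clients also choose which pantries they use, so a comparison at equal exposure is no longer protected by randomisation.

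With the score beside arm in the model, the arm coefficient becomes the difference between arms among clients with the same exposure. That does not undo contamination. Any part of the effect that travels through exposure moves from the arm coefficient to the score's coefficient. If the score includes the home pantry, as the word overall suggests, it also overlaps heavily with arm and the arm effect is poorly estimated. At stake is a confirmatory test that could miss an effect which the plain comparison by arm would show.

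**Working it through.** **1. Inputs from the plan.** The Sample size and power section gives: "sample-size assumed a difference in FAST Scores of 12 points, effect size of 0.8, intraclass correlation of 0.2, type I error of 5"%, with 10 pantries per arm and 18 clients per pantry. I take 20 pantries in total, as in the abstract and the randomisation section, and a two-sided test.

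- SD = 12 / 0.8 = 15.
- Design effect = 1 + (18 − 1) × 0.2 = 4.4.
- SE of the arm difference = 15 × √(2 × 4.4 / (10 × 18)) = 3.32.
- Power of a cluster-level t-test on 18 degrees of freedom = 92.8%.

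The plan's figure of 80% power with 10 pantries is not reproduced exactly. These inputs need 25 × 4.4 / 18 = 6.1 pantries per arm, and the t-test first passes 80% at 8 per arm (85.3%). The stated design is conservative on its own inputs, so the loss described below does not come from a small sample.

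**2. Assumed model.** Let T be arm, E the share of visits made to intervention pantries, h the between-arm difference in mean E, and f the fraction of the effect that runs through exposure:

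outcome change = (1 − f) × 12 × T + f × 12 × E / h + pantry effect + client error.

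The total effect of allocation is (1 − f) × 12 + f × 12 = 12 for every f. In a model with T and E together, the coefficient of T is (1 − f) × 12. The documents give neither f nor the distribution of E, so both are varied.

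**3. Bias.** Simulated trials (1,000 per row) with a random-intercept model of known ICC, critical value 2.101, and an assumed mean home-pantry visit share of 0.8, so h = 0.8:

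| f | (1 − f) × 12 | Simulated arm coefficient with score | SE | Power |
|---|---|---|---|---|
| 0% | 12 | 12.4 | 7.2 | 35% |
| 25% | 9 | 8.7 | 7.2 | 19% |
| 50% | 6 | 6.1 | 7.2 | 10% |
| 75% | 3 | 2.8 | 7.3 | 5% |
| 100% | 0 | 0.0 | 7.3 | 4% |

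Without the score, the same data give 11.8 to 12.2, SE 3.3 and power 92% to 95% in every row. The simulation error of the adjusted mean is about 7.2 / √1000 = 0.23.

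**4. Precision when there is no bias (f = 0).** The arm coefficient stays near 12, but the SE depends on how far exposure overlaps with arm:

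| Assumed exposure | SE with score | Power at f = 0 |
|---|---|---|
| Intervention clients 0.2 to 1; 20% of comparison clients at 0.1 to 0.5 | 3.9 | about 85% |
| Mean home share 0.6 | 4.5 | 72% |
| Intervention clients 0.5 to 1; 20% of comparison clients at 0.1 to 0.5 | 4.9 | about 64% |
| Mean home share 0.8 | 7.2 | 35% (other runs near 0.8: 26% to 30%) |
| Mean home share 0.9 | 14.2 | 12% |

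Hand check for a home share of 0.8: 12 / 7.24 = 1.66, against a critical value of 2.101.

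**5. A score without the home pantry.** When the score counted only visits to other pantries, and those were independent of arm, the arm coefficient was 11.8 to 12.2 in every setting.

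**The case against.** The strongest reply is that the sentence is brief and the article condenses a fuller plan. It does not say that the score enters as a covariate beside arm, when it is measured, or whether the home pantry counts. A score of cross-pantry use would suit the stated purpose, and step 5 shows that such a score can be nearly harmless. This stands in part: the size of the damage depends on a definition that the article does not give. But the complaint is not that a definition is missing. The article commits to adjusting its analyses without limit, beside a hypothesis by allocated pantry. The word overall points to a score that includes the home pantry. Independence from arm is also doubtful, because intervention clients receive a pantry locator: "This feature will show clients where there are food pantries nearby".

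Second, a reader might infer that the adjustment would wipe out the effect. That needs the whole effect to act through pantry exposure, and the documents do not support this. Ordering through eChoice and nutrition messaging act through a client's own app access, which only the selected intervention clients have. A comparison client who visits an intervention pantry does not receive them. Staff training and other pantry-level features could spill over, so partial mediation is plausible. The zero is the end of a range.

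Third, a reader might infer that no comparison by arm alone is planned. One is: the Sample size and power section and the Data analysis section both describe an unadjusted cluster-level comparison of changes. It would appear beside any adjusted result. The Data analysis section, however, places it in the exploratory step, so it does not protect the confirmatory test.

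**Conclusion.** The concern holds in a conditional form. As written, the plan lets a variable that arises after allocation, and that clients choose, into its confirmatory models. This changes what the arm coefficient estimates. With the plan's design inputs, the arm coefficient is about 12, 6 or 0 as 0%, 50% or 100% of the effect runs through exposure. The SE rises from 3.3 to between 3.9 and about 14, depending on how closely exposure follows arm. With no mediation there is no bias, but power still falls from about 93% to between about 85% and 12%.

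These sizes rest on assumed visit shares and mediated fractions, and on a score that includes the home pantry. That the score is measured after randomisation is inferred from its purpose. The simulations do not model self-selection, which could bias the adjusted coefficient in either direction.

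**What to change.** State that the primary confirmatory model compares clients by the randomised arm of their home pantry, with baseline covariates only (for example pantry size, the stratification factor) and no exposure term. Confine the exposure score to a labelled secondary or sensitivity analysis, such as a dose-response description, and say there whether the home pantry counts and when the score is measured. If an instrumental-variable estimate with allocation as instrument is wanted, its exclusion assumption must be stated. That assumption is doubtful here, because app access also acts directly and not only through pantry visits. Report use of other pantries by arm, so that readers can judge the contamination.

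The cost is a change of wording in the analysis plan. No data are lost, and no change to sample size or data collection is needed.

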### Trial evaluation

2.10

The SAFPAS trial will be evaluated at multiple levels, at baseline and post-SAFPAS intervention. The primary outcome is change in client Food Assessment Scoring Tool (FAST) scores of the food received from participating food pantries, and differences in changes in the score between the intervention and comparison groups. We will collect a series of secondary measures at the client, food pantry, food pantry staff and volunteer levels, app feasibility metrics, and process measures outlined. The measures will be collected by trained graduate research assistants and data collectors from the Johns Hopkins Bloomberg School of Public Health. Client-level participants will receive up to $40, food pantry managers/directors will receive up to $20, and food pantry staff/volunteers will also receive $20 up to two times each following data collection at baseline and post-intervention. They will receive this amount in the form of a Visa gift card.

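### The confirmatory mixed models are given two different responses, change and posttest score, with baseline FAST not named as a covariate; one baseline-adjusted model would settle this

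*Protocol article*

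**What the plan says.** All of the model specification stands in one paragraph of section 2.12, Data analysis.

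- Role of the models: "Then we will conduct linear mixed-effect models for confirmatory testing of intervention effects, with adjustments". The t-tests and rank tests that precede them are called exploratory.
- Response, first statement: "The mixed effects regression models will use change in pantry- and client-level scores over time as outcomes".
- Response, second statement, a few sentences later: "Posttest scores will be response variables in the models".
- Covariates: "Adjustments for client demographics (age, sex, education, etc.) and pantry-level variables (e.g., pantry size) will be considered". For contamination between pantries, "we will calculate an overall intervention pantry exposure score and adjust our analyses".
- Clustering: the client's home "pantry will be treated as a random effect".

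Elsewhere the target is change. Section 2.10, Trial evaluation, says "The primary outcome is change in client Food Assessment Scoring Tool (FAST) scores of the food received from participating food pantries", together with the between-arm difference in that change. Section 2.11, Sample size and power, rests on a "cluster-level t-test comparing the mean change in FAST scores of client bags". The primary hypothesis and the expected 12-point advantage in section 2.12 are also worded as change.

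**The concern.** The two response statements describe the same models in general terms. Neither is tied to a particular outcome or to a secondary analysis, so a reader cannot tell which regression yields the confirmatory result for the primary outcome. This is not a detail left to an unseen analysis plan, because the article fixes the response twice, in two ways.

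A baseline term would reconcile the sentences, but the article does not name one. The open-ended part of the covariate sentence refers to client demographics and to pantry-level variables.

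With only 10 pantries per arm, the mean baseline FAST scores of the arms can differ noticeably by chance, and the possible models treat such a difference differently. Unadjusted change subtracts all of it, posttest alone subtracts none, and baseline adjustment subtracts the share that the data support. At stake are precision and the existence of two candidate confirmatory results for one hypothesis.

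**Working it through.** **Inputs from section 2.11:** difference 12 points, effect size 0.8, intraclass correlation 0.2, type I error 5%, power 80%, 10 pantries per arm, 18 clients per pantry. The last two are read as including the stated allowances, so 9 pantries per arm and 15 clients before them. **Assumed:** a two-sided test, equal pre and post variances, and a pre-post correlation r that is the same between and within pantries. The article gives no value for r, so a range is shown.

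**1. The plan's own figure.** The implied SD is 12/0.8 = 15. Without clustering this needs 25 clients per arm. The design effect with 15 clients is 1 + 14 × 0.2 = 3.8, so 25 × 3.8/15 = 6.3, or 7 pantries per arm by the normal approximation. A cluster-level t-test needs 8 (power 0.840; 7 give 0.779). The design has power 0.886 at 9 × 15 and 0.928 at 10 × 18. On this reading the stated inputs exceed 80% rather than reproduce it. The present point does not depend on that.

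**2. Variance of each estimator,** relative to posttest alone = 1 (large samples):

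- change: 2(1 − r)
- posttest adjusted for baseline: 1 − r²
- adjusted relative to change: (1 − r²)/[2(1 − r)] = (1 + r)/2

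Change and posttest alone are equally precise only at r = 0.5. Below that posttest alone is better, and above it change is better.

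**3. Allowing for 20 pantries.** Estimating the baseline slope from N pantry means inflates the adjusted variance on average by 1 + 1/(N − 4). For N = 20 this is 17/16 = 1.0625, a factor of 1.031 on the SE.

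| Assumed r | (1 + r)/2 | SE ratio to change, large sample | SE ratio × 1.031 | SE reduction, large sample / 20 pantries |
|---|---|---|---|---|
| 0.3 | 0.65 | 0.806 | 0.831 | 19% / 17% |
| 0.5 | 0.75 | 0.866 | 0.893 | 13% / 11% |
| 0.7 | 0.85 | 0.922 | 0.951 | 8% / 5% |

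Simulation with 20 pantries of 18 clients gave the same 17%, 11% and 5%. At r = 0.9 the variance ratio is 0.95 × 1.0625 = 1.01, so there is no gain over change. Against posttest alone at r = 0.2 it is 0.96 × 1.0625 = 1.02, so there is no gain there either.

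**4. SEs in FAST points,** simulated with 9 pantries per arm, 15 clients each and a score SD of 15 (borrowed from 12/0.8):

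| r | Change | Posttest alone | Adjusted |
|---|---|---|---|
| 0.2 | 4.49 | 3.53 | 3.58 |
| 0.5 | 3.56 | 3.55 | 3.20 |
| 0.8 | 2.24 | 3.55 | 2.21 |
| 0.9 | 1.58 | 3.55 | 1.59 |

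**5. Chance baseline imbalance.** With 10 pantries of 18 clients per arm, the SD of the arm difference in baseline is √[(2/10)(0.2 + 0.8/18)] = 0.22 score SDs, or 0.22 × 15 = 3.3 points if the score SD is 15. Posttest alone carries a share r of any realised difference on average.

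**6. Disagreement under the null** (20 pantries of 18 clients, intraclass correlation 0.2, 20,000 runs per r):

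| r | Tests disagree on significance | Type I error if the better is taken |
|---|---|---|
| 0.3 | 7.8% | 8.9% |
| 0.5 | 8.1% | 9.1% |
| 0.7 | 8.7% | 9.3% |

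The columns agree with each other. At r = 0.5, both tests reject in 9.1 − 8.1 = 1.0% of trials, and 5 + 5 − 1.0 = 9.0% is the chance that at least one rejects.

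**7. Why a baseline term removes the conflict.** If posttest = a + τ·arm + b·baseline + pantry effect + error, subtracting baseline from both sides gives change = a + τ·arm + (b − 1)·baseline + pantry effect + error. Only the baseline slope changes; τ is the same. In simulation the two estimates of τ differed by at most about 2 × 10⁻¹⁴.

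**The case against.** The strongest reply is that the intended contrast is clear. The primary outcome, sample size, hypothesis and expected effect are all worded as change, and one sentence departs from them. A posttest response is commonly paired with a baseline covariate, the models are to be adjusted, and the covariate lists are given as examples. If baseline was meant to be included, the two sentences lead to the same intervention effect. Unadjusted change would also be valid by itself and matches the sample-size test.

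Most of this stands. Failing to name baseline FAST does not show that it is excluded, and the contradiction could be ended simply by choosing one response. What remains is that the article never states the reconciling term, and the inconsistency sits in the models it calls confirmatory.

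Three stronger readings are tempting and are not supported:

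- *A posttest-only model is biased or misses the hypothesis.* Under randomisation the arms have the same expected baseline, so posttest and change have the same expected arm difference. In simulation each test alone kept its type I error near 5% (0.046 to 0.054). Chance imbalance is already reflected in the standard error.
- *The plan has a 9% type I error.* That needs both unadjusted models to be fitted and the more favourable one reported. The article describes no such selection.
- *Baseline adjustment is always clearly more precise, because the pre-post correlation must be modest.* The article gives neither a correlation nor the number of bags per assessment. The gain depends on r and disappears at the ends of the range shown.

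**Conclusion.** The contradiction is real, stands in the current text and affects the confirmatory analysis of the primary outcome. It concerns which estimator is used, with what precision, and whether the analysis is fixed in advance; it is not a matter of bias. Left open, it allows two confirmatory answers that would differ on significance in about 8% of null trials, with about 9% type I error as the worst case.

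Baseline adjustment removes the ambiguity at any r. Its precision gain over unadjusted change, 17% to 5% of the SE for r from 0.3 to 0.7 with 20 pantries, rests on an assumed correlation, equal variances and the stated intraclass correlation of 0.2. It should be presented as likely rather than guaranteed. The planned sample size need not change on this account.

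**What to change.** State one primary model in section 2.12: posttest FAST (or, equivalently, change in FAST) on arm, the client's baseline FAST, pantry-size stratum (the stratification factor in section 2.5) and a random pantry effect. Pantry-mean baseline FAST may be added but is optional. Name one response and remove the competing sentence. Keep unadjusted change, if wanted, as a labelled sensitivity analysis. The hypothesis can stay worded as a difference in change, because the arm coefficient still estimates the 12-point contrast.

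The change is one of wording, to be made before outcomes are analysed by arm. Baseline FAST is already collected. The statistical cost is one or two of the 18 pantry-level degrees of freedom (20 − 2).
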